### Concealment mechanism {16b}

The allocation of treatment is hidden from both participants and investigators. Upon enrolment, participants are notified by the investigator that they will be allocated to one of two treatment groups according to an allocation list generated by a computerised system. Each participant will have the same probability of receiving either treatment. This sequence list is adjusted to the participant’s arrival time for the baseline examination at the hospital. The nurse assistant will keep the record list and determine the treatment received based on the numbered sequence list.

### Implementation {16c}

After a non-research team member generates participant sequences from a computer programme, a nurse assistant as an administrator at the outpatient clinic will maintain their records. Each participant will be assigned a code number, and the code generated by the computer programme will determine the type of intervention they received. The nurse assistant will also have access to the patient’s identity and code number.

## Assignment of interventions: blinding

### Who will be blinded {17a}

The outcome assessors and data analyst will be blinded to the treatment assignment. The assessors will evaluate the clinical changes such as the POSAS scores and degree of erythema and pigmentation, as well as the area, thickness, and pliability of the keloid. As the intervention’s nature makes it impossible to blind participants and staff to the allocation, they are instructed not to disclose the participant’s allocation status during follow-up assessments. A computer IT assistant and other outcome assessors who assess the POSAS score and the degree of erythema and pigmentation, area, thickness, and pliability of keloid will anonymously be blinded to the intervention. They will record the results in anonymously case report forms (CRFs) and input data into separate datasheets online. This will enable the researcher to analyse data without accessing information about the allocation.

### Procedure for unblinding if needed {17b}

The outcome assessors are blinded to the interventions. Unblinding will be necessary should the assessors identify any severe adverse events, such as allergic or irritant reactions. The findings will be communicated to the investigators and The Medical and Health Research Ethics Committee (MHREC). The MHREC may permit unblinding if required. Nevertheless, unblinding is not necessary for minor adverse events, such as temporary pain, itchiness, or transient erythema. Unblinded participants who experience severe adverse events will not be excluded from the analysis, but they will be removed from ongoing treatment.

## Data collection and management

### Plans for assessment and collection of outcomes {18a}

For the primary outcome, the evaluation analyses change in POSAS 3.0 scores over four periods, from the initial baseline to the final assessment conducted by a trained and blinded dermatologist to the interventions. After each review, a nurse assistant will collect the completed POSAS 3.0 forms attached in a CRF, and another non-research team member will input data online into an online form directly to the data analyst. The patient and observer scar assessment scale (POSAS) is a practical, comprehensive, and reliable measurement tool involving the perspectives of patients and doctors [57–59].

There are several measurements for secondary outcomes. A proficiently trained assistant, blinded to the intervention, will utilise dermoscopy to capture the colouration of the keloid. Subsequently, these images will be anonymously forwarded to a computer IT assistant for assessment of the degree of erythema and pigmentation using the ImageJ image analysis programme. After each process, the results will be recorded in a CRF and sent via an online form without any identifiable intervention to the data analyst. Measuring colours using ImageJ is comparable to measuring colour with a colourimeter [60, 61]. Taking pictures using a dermoscopy is not affected by distance and lighting because the dermoscopy has a fixed shooting distance and polarised lighting that comes directly from the device itself, so the pictures taken are more accurate than those that use a camera. Dermoscopy is a valid and reliable method for assessing the colour of both pigmentation due to the presence of melanin pigment and erythema caused by increased vascularity of scar tissue [62].

A trained personnel will acquire a surface area photograph using a digital single-lens reflex (DSLR) camera and subsequently transmit it anonymously to the computer IT assistant. The IT assistant will then utilise the ImageJ image analysis tool to ascertain the measurement, yielding an average value in millimetre squares, which will be meticulously documented in a CRF. This information will be subsequently transmitted to an online form accessible solely by the data analyst, who will be granted access exclusively to the participant code while remaining uninformed about the intervention particulars. The change surface area with photographic planimetry is reliable for assessing an area of approximately or equal to 25 cm^2^ [63]. Pictures were taken using a versatile single-lens reflex camera that can capture better-quality images than other types of cameras [64]. In measuring the area of the wound, this device provides fast, accurate results and good reliability [65].

Keloid thickness in millimetres is assessed through high-frequency ultrasound (HFU) conducted by an intervention-blinded radiologist, utilising solely the participant’s code number in a designated CRF. Following this, the obtained data will be compiled by a nurse assistant, and the data entry process into an online form will be conducted by a non-research team member, who will subsequently transmit it to the data analyst for further analysis. The high-frequency ultrasound method is a non-invasive, affordable, and valuable method for evaluating the clinical efficacy of scar tissue treatment [66–69].

A trained assistant will measure the pliability of the keloid using a durometer type oo from three different areas. The result will be recorded in a CRF, and a non-research member will input the data into an online form to the data analyst without any known intervention. The tool will undergo routine calibration. Tissue tonometry is a simple, repeatable, and objective method of measuring tissue density and is clinically useful for assessing individual scar tissue [70–72].

### Plans to promote participant retention and complete follow-up {18b}

To ensure participants’ continued involvement, we will highlight the clinical advantages of participating in the study and provide transportation fees to alleviate any financial burden of attending examinations. Our research administrator will send patients reminders 2 days before their scheduled visit and reschedule if they cannot make it at the arranged time.

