### Provisions for post-trial care {30}

Any side effects during the study will be treated as they would in a clinical setting. The serious adverse event form will document any risks beyond minimal or physical injury. If a serious adverse event is found to be causally linked to the research intervention, it will be addressed according to applicable procedures. If the participants derive significant benefits from the new drug intervention, they can continue receiving the treatment as long as the gels are available. Similarly, suppose subjects benefit from the intralesional injection, the active control, and wish to continue with the therapy. In that case, it will be extended for approximately two months after the study concludes.

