### Outcomes {12}

The research inquiry will encompass an assessment of both primary and secondary outcomes. The primary outcome directed towards the evaluation of POSAS 3.0 scores. Throughout the study’s duration, we will systematically assess POSAS 3.0 scores at four specific time intervals: the initial baseline assessment upon participants’ first arrival, followed by subsequent evaluations at weeks 4, 8, and 12. This measurement directly correlates with the patient’s quality of life [52]. We will utilise the most up-to-date version of the POSAS 3.0 questionnaire, accessed at https://www.posas.nl. We have received approval from the POSAS team to use this questionnaire and have been granted a license via email. This questionnaire will be translated into Indonesian and tested for validity and reliability before being used in the study. Patients will complete the POSAS 3.0 questionnaire, which includes 16 items. Five of these items are about the current state of their scar tissue, and 11 questions are about how their feeling related to the scar tissue over the past week. Meanwhile, an observer will complete a different section of the questionnaire with seven items scored on a scale of 1 to 5. We will add the PSAS and OSAS scores to determine the total score. The minimum patient score is 16, while the highest score is 80. The minimum and maximum scores for observers are 7 and 35, respectively.

In the context of this study, secondary outcomes encompass the evaluation of erythema and pigmentation levels, as well as assessments of keloid area, thickness, and pliability. These secondary outcome measures at four different time points will be assessed concurrently with the primary outcome.

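### The retention message and the benefit-dependent post-trial offer add an avoidable, minor risk to the unblinded self-ratings that form most of the primary POSAS total

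*Protocol article*

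**What the plan says.** Under blinding, section {17a} of the protocol article accepts that the intervention's "nature makes it impossible to blind participants and staff to the allocation". Outcome assessors and the data analyst are blinded.

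Section {12} makes POSAS 3.0 the primary outcome. For the patient part, "Patients will complete the POSAS 3.0 questionnaire, which includes 16 items"; for the other part, "an observer will complete a different section of the questionnaire with seven items scored on a scale of 1 to 5". The two are then summed: "We will add the PSAS and OSAS scores to determine the total score".

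Two rules on conduct bear on the patient part:

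- **Retention, {18b}.** To keep participants involved, "we will highlight the clinical advantages of participating in the study". Transport fees and visit reminders are offered as well.
- **Post-trial care, {30}.** For the gel: "If the participants derive significant benefits from the new drug intervention, they can continue receiving the treatment as long as the gels are available". For the injection, a participant who benefits and wants to go on may do so, and "it will be extended for approximately two months after the study concludes".

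Section {30} does not say who judges benefit or by what measure.

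**The concern.** Open treatment cannot be avoided when a gel is compared with an injection, so unblinded self-rating is not itself the complaint. The two rules are avoidable, and both act on people who know their arm and score their own scar.

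The {18b} message tells participants that taking part has clinical advantages while the trial is still measuring clinical change. The {30} rule gives a participant who wants to keep the treatment a reason to report that it worked. Participants who know their arm need not respond equally to either. The access terms differ by arm: the benefit wording is stronger for the gel, and the gel offer lasts while supply does, against about two months for the injection. The gel is supplied as a study product by one company ({11a}), whereas triamcinolone injection is already widely used in Indonesia ({6a}).

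Any differential response would enter the primary comparison through the patient items, and blinding the observer and the analyst would not remove it. A positive result could then be attributed partly to promotion and access.

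**Working it through.** **Inputs.** From {14}: SD 4.8, target difference 4 points, z-values 1.96 and 0.84, repeated-measures factor Y = 0.8, dropout 20%. From {12}: 16 patient items (range 16 to 80) and 7 observer items (range 7 to 35). The size of any rating shift is not in the document, so it is assumed below.

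**1. The plan's own figure.** n = Y × 2 × [(1.96 + 0.84) × 4.8 / 4]² = 0.8 × 2 × 3.36² = 18.06, stated as 18. With dropout, 18 / (1 − 0.2) = 22.5, rounded up to 23. Both stated figures reproduce.

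**2. Weight of the self-ratings.** Items: 16/23 = 69.6%. Range: (80 − 16) / [(80 − 16) + (35 − 7)] = 64/92 = 69.6%.

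**3. Shift per item that equals the target.** Over all 16 patient items, 4/16 = 0.25 point. If only the 11 items on feelings moved, 4/11 = 0.36 point.

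**4. Effect on the type I error.** On the plan's own variance, the effective SD is 4.8 × √0.8 = 4.293. The standard error of the difference is 4.293 × √(2/n), which is 1.266 at 23 per arm and 1.431 at 18 per arm. With no true effect and a differential reporting shift of b points,

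P(p<0.05) = 1 − Φ(1.96 − b/SE) + Φ(−1.96 − b/SE).

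For b = 1 at 23 per arm: b/SE = 0.790, so P = 0.121 + 0.003 = 0.124. For b = 2: b/SE = 1.580, so P = 0.352.

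| Differential shift b (points) | Per patient item (b/16) | P(p<0.05), 23 per arm | P(p<0.05), 18 per arm |
|---|---|---|---|
| 0 | 0 | 5% | 5% |
| 1 | 0.0625 | 12% | 11% |
| 2 | 0.125 | 35% | 29% |
| 4 | 0.25 | 88% | 80% |

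**5. Equal shift.** If both arms shift by the same amount, b = 0 and the error rate stays at 5%. Only a difference between arms matters.

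The table shows how sensitive the design is to a differential shift. It does not estimate how large a shift these two rules would cause.

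**The case against.** The case on the other side is strong, and most of it stands.

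- **The message is not about the gel.** {18b} speaks of taking part and draws no distinction by arm. Both arms receive active treatment, one of them the recommended standard, so participation can have clinical advantages without any claim for the gel. This stands.
- **The post-trial rule does not mention POSAS.** {30} names no instrument and no judge, and does not say that participants hear the condition before they rate. Continuing a treatment only where it helps is ordinary care and applies to both arms. Under {18a} the forms pass from a nurse assistant to a non-research team member, who enters the data for the analyst; nothing routes the answers into a treatment decision. This stands, with one limit: under {16c} the nurse assistant can link code to identity, so the separation is partial.
- **There are checks on self-report.** The observer items, colour, area, thickness and pliability are assessed blind, so an effect confined to self-report could be seen against them. This stands, but the primary total still sums both parts.
- **An article leaves scripts and information sheets to the full protocol.** True of detail, but the content of the message and the benefit condition are stated here and can be judged as stated.

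A reader might infer that the two rules push ratings towards the gel in particular. The document does not support that. The different access terms make such a direction plausible, but a gel offer limited by supply could last longer or shorter than two months. Wide use of triamcinolone does not show that injections provided by the trial are valued less.

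**Conclusion.** The point holds as a minor one. Two stated and avoidable rules add a risk of expectation or incentive effects to self-ratings that make up about 70% of the primary score. A between-arm bias, and its direction, are not established.

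The size is conditional. A differential shift of 0.25 point per patient item would match the whole 4-point target, and an assumed shift of 1 or 2 points would raise the false-positive chance from 5% to about 12% or 35% at 23 per arm. These figures rest on the plan's own SD and factor Y, on no true effect, on a normal approximation, and on the whole shift being between arms. The sample size is not in question here.

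The reason to act is that the change costs almost nothing and removes an argument against a positive result.

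**What to change.** In {18b}, replace the message about clinical advantages with one neutral script used in both arms: complete data matter whatever the result, and it is not known which treatment is better. Keep the transport fees and reminders.

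In {30}, state that POSAS answers play no part in post-trial access, tell participants so, and discuss continuation only after the week-12 form has been handed in. Leave the post-trial treatments and their terms unchanged.

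The cost is some rewording of the retention script, the explanatory sheet and the post-trial section. The downside is a slightly weaker retention message.

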### Data management {19}

The computer IT assistant who does image analysis and a non-research team member will send data directly to data analysts online, ensuring anonymity and intervention blind. This will be done through a specific code entered into an online form spreadsheet. Any hard copies of the data, including CRFs, will be securely stored in a data bank at the hospital. The data analyst will double-check the completeness and clarity of the data by verifying that it matches the initial data in CRFs.

### Confidentiality {27}

Before signing the consent form, all potential and enrolled participants will receive an explanation sheet detailing the use of their personal information in this study. The explanation will emphasise the confidentiality of their identity, and the research staff will request their name and contact information solely for study purposes. However, their name will not be used in any published results. Instead, each participant will be assigned a unique code as a replacement identity. Any study results may be published in scientific literature, but the participants’ names or identifying information will be excluded. It should be noted that sponsors, the ethics committee of Universitas Gadjah Mada, or the researchers conducting the study may have access to the data obtained from the research. Nevertheless, the supervisor has the legal authority to protect all identifiable information from public disclosure unless required by law or a competent court. These notes will be kept confidential per the law and stored in the data bank of the general hospital of Syafira.

### Plans for collection, laboratory evaluation, and storage of biological specimens for genetic or molecular analysis in this trial/future use {33}

Not applicable. No involvement of any biological specimens.

## Statistical methods

### Statistical methods for primary and secondary outcomes {20a}

Statistical analysis will be done by Statistical Package for Social Science (SPSS) version 24. An analysis of the demographic data of the research subjects is planned to be conducted using descriptive statistics. The findings presentation will utilise frequency and percentage tables. Mean values are presented with standard deviation for continuous variables with a normal distribution. The normality of the data can be determined using the Shapiro-Wilk test. If the distribution is not normal, the median and interquartile range (IQR) are used. We conduct an analysis that compares the efficacy of a numerical variable in two groups and within a group, measured multiple times, using a generalised linear model analysis with alternative repeated Mann-Whitney analysis. Our study focuses on continuous variables for both primary and secondary outcomes. Our test had a power value of 80%, a confidence interval of 95% (95% CI), and a significance level of *p* < 0.05.

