### Sample size {14}

The sample size determination depends on the specific criteria for comparative research. The variable type of the primary outcome data plays a significant role in deciding the appropriate sample size [50, 51, 53, 54]. The primary outcome is the changes in POSAS 3.0 scores, considered continuous data. Effect size measurement will be the mean difference. The research involved unpaired or two groups receiving different treatments, with the outcome being measured multiple times. As a result, a specific formula was utilised below [55].

This study maintains a 5% type I error dan is powered to have an 80% chance of detecting a minimum of 4 different scores of POSAS. Thus, a sample size of 18 was calculated for the two-sided approach. Adjusted sample size to anticipate a 20% dropout is obtained from the formula N1 = *n*/(1-d), with *n* as the sample size required per formula and d as the dropout rate [56]. Thus, the final sample will be 23 for each group treatment.$${n}_1={n}_2=Y\left[2{\left(\frac{\left[{z}_{\alpha }+{z}_{\beta}\right]s}{x_1-{x}_2}\right)}^2\right]$$

*Z*
_*α*_ = 5% (1.96), *Z*_*β*_ = 20% (0.84), *S* (standard deviation) = 4.8, *x*1-*x*2 (the minimum difference in POSAS scores between the two treatment groups) = 4, *Y* (correction factor for multiple assessments) = 0.8.

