### Methods in analysis to handle protocol non-adherence and any statistical methods to handle missing data {20c}

Our analysis will involve intention-to-treat analysis (ITT) to address non-adherence among participants, along with multiple imputations to handle any missing data. Additionally, we will thoroughly report the reasons for withdrawal within each randomisation group and qualitatively compare them. To ensure accuracy, we will combine all completed and imputed datasets and utilise Rubin’s multiple imputation method with five datasets to estimate the treatment effect.

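### Two different analyses are named for the primary outcome, a generalised linear model and repeated Mann-Whitney tests, with no rule for choosing between them

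*Protocol article*

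**What the plan says.** Section {20a} of the protocol article first covers description: means with standard deviations for normal variables, then "The normality of the data can be determined using the Shapiro-Wilk test", then medians with interquartile ranges for the rest. A separate sentence turns to efficacy. It names a generalised linear model for the comparison between and within groups over repeated measurements, "with alternative repeated Mann-Whitney analysis". The section goes on to say that primary and secondary outcomes are continuous, so the pair of methods covers both. It also promises a 95% confidence interval. It does not say when the alternative replaces the model.

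Two other sections depend on which method is used:
- Sample size {14}: "Effect size measurement will be the mean difference". The trial is "powered to have an 80% chance of detecting a minimum of 4 different scores of POSAS".
- Missing data {20c}: the analysis will "utilise Rubin’s multiple imputation method with five datasets to estimate the treatment effect".

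**The concern.** A primary analysis should be fixed before the data are seen. Here two methods stand side by side, and they test different hypotheses and report different things. Two readings are possible:
- **Shapiro-Wilk is not the trigger.** Then no trigger is stated, and the choice is free after results are known.
- **Shapiro-Wilk is the trigger.** Then a pre-test on the trial's own data picks the primary test. The level of that pre-test, the data it is applied to (scores, changes or residuals; by arm or by visit) and the way several results combine are all unstated.

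At stake are which null hypothesis is tested and whether the primary result appears in POSAS points that can be set against the planned difference of 4. The single treatment effect that the imputation section intends to pool is also at stake.

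**Working it through.** **1. What the trial is sized on.** Inputs from Sample size {14}: "This study maintains a 5% type I error", two-sided (1.96), 80% power (0.84), SD 4.8, difference 4, correction factor 0.8, dropout 20%.

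n = 0.8 × 2 × [(1.96 + 0.84) × 4.8 / 4]² = 1.6 × 3.36² = 18.06, stated as 18. Then 18 / (1 − 0.2) = 22.5, stated as 23. Both figures reproduce. This is a calculation for a difference in means and contains nothing about a rank test.

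**2. Chance of switching with exactly normal data, if Shapiro-Wilk were the trigger.** Assumptions that the article does not state: each test is at 0.05 and any single rejection switches the method. With k independent tests the chance is 1 − 0.95^k. Correlated visits were also simulated (18 and 23 per arm, between-visit correlation 0 to 0.9, 3,000 runs per setting).

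| What is tested | k | 1 − 0.95^k | Simulated |
|---|---|---|---|
| Residuals of week-12 change, once | 1 | 5.0% | about 5% |
| Week-12 change, each arm | 2 | 9.8% | 9–11% |
| Residuals at each of four visits | 4 | 18.5% | 15–19% |
| Change at three visits, each arm | 6 | 26.5% | 25–27% |
| Raw scores, four visits, each arm | 8 | 33.7% | 26–36% |

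With skewed data the spread is wider. Simulated with 23 per arm and an assumed correlation of 0.6, the eight-cell rule switches in about 60% of trials at skewness 0.5 and 94% at skewness 1. The two-test rule on week-12 change switches in 12% and 22%.

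**3. Does validity require the switch?** Same setting, no true difference, and data that were normal, of skewness 0.5 or of skewness 1. A t comparison of mean change rejected in 4.5% to 5.2% of trials across two separate simulations (2,000 and 3,000 trials per setting). The mean comparison holds its level in all three cases.

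**4. What the alternative delivers.** Mann-Whitney tests repeated by visit give one p-value per visit. They do not by themselves give a mean difference in POSAS points. Rubin's rules need one estimate and its variance from each imputed dataset, and a set of p-values does not supply that. If significance at any one of the three follow-up visits counts as success, the simulated type I error is 12% to 13% (1 − 0.95³ = 14.3% if the visits were independent).

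**5. Is that inflation due to the normality test?** No. With no pre-test at all, t tests at three visits with any one counting give 12.5% to 12.8%, and Mann-Whitney gives about 12%. When both routes test the same single quantity and the eight-cell rule picks the route, the error stays near 5%: 4.6% / 4.8% / 4.6% for week-12 change and 5.2% / 4.7% / 5.1% for mean change (normal / skewness 0.5 / skewness 1). The two tests then disagree on p < 0.05 in only 1.7% to 2.9% of null trials.

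**The case against.** The strongest case on the other side has four parts.

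- **The gate is inferred.** The Shapiro-Wilk sentence sits between two sentences on descriptive presentation, and its only stated consequence is the choice of summary. A reader might infer that it decides the primary analysis, but the article does not say so. This stands.
- **The switch rate is assumed.** A reader might also infer that about a third of trials with normal data would switch. That needs eight raw-score tests at 0.05 with any rejection decisive. The primary outcome is change in score, so the baseline cells need not be tested at all. This stands: only the range of 5% to about 34% can be supported.
- **The pre-test does little harm to type I error.** Step 5 of the working confirms this. Blaming Shapiro-Wilk for the inflation would be wrong.
- **Nothing says that the mean difference would be dropped.** The effect measure, the confidence interval and the pooled estimate are promised without condition, and an article may leave details of tests and triggers to a fuller document. The first half stands, so it goes too far to say that the effect estimate would be lost.

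The last part does not dispose of the point. The article is not silent on the primary method. It names two, and the second does not by itself produce what the sample size and missing-data sections rely on.

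**Conclusion.** The point holds as an unfixed choice between two primary analyses. That is certain from the text and rests on no simulation.

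The size of any chance switching is conditional. If Shapiro-Wilk at 0.05 is the trigger, it runs from about 5% (one test) through 10% (two) and 26% (six) to about 34% (eight) with normal data. The 12% type I error for repeated Mann-Whitney tests is also conditional: it assumes that any follow-up visit can count, and it is a multiplicity effect. The finding that the mean comparison keeps its level assumes 23 per arm, a between-visit correlation of 0.6 and skewness of at most 1.

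The main costs are the freedom to choose the method and the risk of a primary result with no effect in POSAS points. The plan should be changed because the remedy is cheap, although nothing here shows that the linear model itself would give a wrong answer.

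**What to change.** In section {20a}, name the repeated-measures linear model of change in total POSAS, reported as a mean difference with its 95% confidence interval, as the primary analysis whatever Shapiro-Wilk shows. Keep Mann-Whitney only as a labelled sensitivity analysis that cannot replace the primary result. Apply the same rule to the secondary outcomes. Shapiro-Wilk may still guide the descriptive summaries. This brings the analysis into line with the effect measure in section {14} and the pooled estimate in section {20c}.

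Fixing the model does not settle which visit or contrast carries the primary conclusion. Step 5 of the working shows that t tests with any visit counting inflate the error just as much.

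The cost is one paragraph of wording, with no extra participants, visits or data. The downside is slightly less power than a rank test if the data are strongly skewed.

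### The methods named in {20a} do not, as worded, fit repeated measurements: the model carries no within-participant correlation, and Mann-Whitney cannot make the paired within-group comparison

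*Protocol article*

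**What the plan says.** Section {20a} is the only place in the protocol article that names an inferential method for the primary outcome. The analysis "compares the efficacy of a numerical variable in two groups and within a group, measured multiple times, using a generalised linear model analysis", and the fallback follows in the same sentence: "with alternative repeated Mann-Whitney analysis". Both the between-group and the within-group comparison are therefore given to the model, and Mann-Whitney is the alternative for both. No participant effect, repeated factor or working correlation is mentioned. The software is fixed: "Statistical analysis will be done by Statistical Package for Social Science (SPSS) version 24".

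Outcomes {12} has POSAS 3.0 scored at baseline and at weeks 4, 8 and 12. Sample size {14} defines the primary outcome as the change in POSAS score and allows for repetition through a factor Y ("correction factor for multiple assessments) = 0.8"). Section {20c} plans an intention-to-treat analysis with five imputed datasets combined by Rubin's method.

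**The concern.** Four scores from one person are correlated. A generalised linear model without a participant term or working correlation treats them as independent, so its standard errors are wrong. The direction depends on the effect that is read: an arm effect averaged over visits looks too certain, and an arm difference in change looks too uncertain. The article does not say which effect carries the superiority claim, so either error is possible.

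The fallback has a separate fault. Mann-Whitney compares two independent samples. Comparing one arm's baseline with its own week 12 is a paired problem, and the sentence in {20a} covers that comparison too.

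At stake is whether the primary test has its stated 5% level and 80% power.

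**Working it through.** **Inputs from the document.** Two-sided 5% (z = 1.96), 80% power (z = 0.84), "standard deviation) = 4.8", a 4-point difference, Y = 0.8, 20% dropout, 23 per arm, and four assessments of which three are after baseline. **Assumed, because the document does not give it:** the within-participant correlation ρ, taken as equal between all visits and varied from 0.3 to 0.8.

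**1. The plan's own figure.** 2 × [(1.96 + 0.84) × 4.8/4]² = 2 × 3.36² = 22.58. Times 0.8 gives 18.06, stated as 18. Then 18/(1 − 0.2) = 22.5, rounded up to 23. The figures reproduce.

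**2. Level of a test that ignores the correlation.** Let R be the true variance divided by the variance the model assumes. Then the level is 2 × [1 − Φ(1.96/√R)].
- Arm effect pooled over m visits: R = 1 + (m − 1)ρ, so R = 1 + 2ρ for three visits.
- Arm-by-visit contrast (difference between arms in change between two visits, from raw scores): R = 1 − ρ.

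| ρ | Pooled arm effect, 3 visits | Arm-by-visit contrast |
|---|---|---|
| 0.3 | 12.1% | 1.9% |
| 0.5 | 16.6% | 0.56% |
| 0.6 | 18.6% | 0.19% |
| 0.7 | 20.6% | 0.04% |
| 0.8 | 22.4% | 0.001% |

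Simulation at 23 per arm agrees. At ρ = 0.3, 0.5 and 0.7 the pooled effect ran at 11.5%, 16.7% and 20.5%, and the baseline-to-last-visit contrast at 2.0%, 0.7% and 0.07%. In the same model, the arm contrast at one visit alone stayed at about 5%.

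**3. Cost in power for the change contrast.** Suppose, as an assumption, that 4.8 is the SD of change. SE = 4.8 × √(2/23) = 1.415, and 4/1.415 = 2.83. With the correct SE, power is Φ(2.83 − 1.96) = 81%. Ignoring correlation raises the effective critical value to 1.96/√(1 − ρ):
- ρ = 0.3: 2.34, power 69%
- ρ = 0.5: 2.77, power 52%
- ρ = 0.7: 3.58, power 23%

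**4. Mann-Whitney, simulated at 23 per arm, for ρ = 0.3, 0.5, 0.7.**
- Baseline against week 12 within one arm, treated as unpaired: 1.9%, 0.7%, 0.07%.
- Between arms at week 12: 5.0%, 4.6%, 4.8%.
- Between arms at each of three visits, any one significant: 13.2%, 11.5%, 10.7% (three independent tests would give 1 − 0.95³ = 14.3%).

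**The case against.** The strongest reply is that the sentence is loose rather than wrong. It says the outcome is measured repeatedly, and {14} corrects for that, so the authors plainly knew the data were correlated. They may have meant a general linear model for repeated measures or a generalised estimating equations fit. That model's need for every visit to be present is met by the imputation in {20c}. On that reading none of the model error rates applies. This stands as a limit on the figures, but it does not rescue the wording: the named model is a different one, and the choice governs the primary test.

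A condensed article may also leave the covariance structure and degrees of freedom to an analysis plan. That is accepted, and their absence is not the point. The point is the method the article does name.

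Four stronger readings are tempting, and the document does not support them.
- **Mann-Whitney is the assigned within-group test.** It is the alternative to the model for both comparisons. Used between arms at one visit, it takes one value per participant and makes no assumption about independence across visits.
- **The primary test will run at around 20%.** That needs the literal model, an assumed ρ and a pooled arm effect. No section names the pooled effect as primary. The outcome in {14} is change, for which ignoring correlation is conservative.
- **The sample size itself proves ρ is about 0.7.** If Y is read as [1 + (m − 1)ρ]/m, then 0.8 gives ρ = 0.70 for three visits or 0.73 for four, but Y is not defined that way. Under equal correlation, changes from a common baseline correlate at 0.5, which would give Y = (1 + 2 × 0.5)/3 = 0.67, not 0.8.
- **The superiority conclusion would reverse.** Nothing in the document shows that.

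**Conclusion.** The point holds as a defect in the named methods. Followed to the letter, {20a} gives a model without within-participant correlation and a fallback that is invalid for the within-group comparison. The distortion is conditional:
- about 12-22% for an arm effect pooled over three post-baseline visits (ρ 0.3-0.8)
- about 1.9% to 0.04% for an arm-by-visit contrast (ρ 0.3-0.7), with the matching loss of power
- about 0.07-1.9% for an unpaired Mann-Whitney within a group
- 11-13% for any significant between-arm Mann-Whitney over three visits

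These rest on an assumed ρ and equal correlation between visits. The power figures also take 4.8 as a change-score SD, which {14} does not state. If a repeated-measures model was intended, the model figures fall away and what remains is a wording error in the only sentence that fixes the primary analysis. It should be settled before any data are analysed.

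**What to change.** In {20a}:
- Replace the generalised linear model with a linear mixed model for repeated measures (the MIXED procedure in SPSS), with arm, visit and arm-by-visit as fixed effects and visits correlated within participant.
- Name the difference between arms in change from baseline to week 12 as the primary test.
- For any within-group comparison, use the model's own contrasts or a paired test such as the Wilcoxon signed-rank test.
- Keep Mann-Whitney only for a between-arm comparison of change at the named visit.

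The model can be fitted in each of the five imputed datasets and combined by Rubin's method, as {20c} already plans. If a repeated-measures general linear model was what the authors meant, they should at least say so in place of the present term.

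The cost is a few sentences, with the same data and software. The downside is that covariance parameters must be estimated from 46 participants: an unstructured matrix has 6 for three visits or 10 for four, and compound symmetry has 2.
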